#### PRP preparation

2.3.3

PRP products will be prepared according to the manufacturer’s instructions for the device (JZK-8, China) using a double centrifugation protocol (Figure 2). All centrifugation procedures will be performed at 25 °C to ensure the stability of PLT and leukocyte activity. Peripheral blood (20 mL) will be collected from patients into a tube containing an anticoagulant (acid citrate sodium citrate solution) under sterile conditions. Subsequently, the anticoagulant will be gently mixed with the whole blood before transferring it to centrifuge tubes. The PRP preparation method will be chosen according to the allocated group. Finally, 2 mL of PRP will be collected for clinical application in patients with RCI.

**Figure 2 fig2:**
[figure not shown]
Preparation of the two types of PRP.. Created with BioRender.com.

##### Group1: low-PLT LP-PRP

2.3.3.1

The entire tube will be placed into a secondary device supplied by the same manufacturer for the first centrifugation at 1200 rpm for 10 min, and three layers—the upper plasma layer, the middle buffy coat layer, and the lower red blood cell layer—will be observed in this process. To minimize the leukocyte effect, only the upper 80% of the plasma layer will be drawn and transferred to a new tube, avoiding the buffy coat and red blood cell layers. The plasma and PLT will be re-centrifuged at 3000 rpm for 15 min to maintain the bottom PLT layer, ultimately yielding approximately 2 mL of PRP.

##### Group 2: high-PLT LR-PRP

2.3.3.2

The first centrifugation will be performed at 1500 rpm for 10 min with three layers. The plasma and PLT, including the buffy coat, will be drawn into a new sterile tube and re-centrifuged at 2500 rpm for 10 min. Two-thirds of the upper platelet-poor plasma (PPP) will then be removed, retaining the bottom PLT concentrate to yield approximately 2 mL of PRP.

#### Injection procedure

2.3.4

A 2 mL mixture of 2% lidocaine and 0.9% normal saline (1:1 ratio) will be injected using a 25-gauge needle to separate the adherent bursa and anesthetize the rotator cuff tendon. The anesthetic effect will be limited to the needle insertion path and will not extend to the wider area surrounding the target injury region. After the local lidocaine injection, PRP will be administered 1–2 min later to avoid high concentrations of anesthetics remaining in the needle tip channel. To achieve optimum efficacy, the injection strategy will be designed according to MRI findings and clinical signs indicating the origin of the pain. To control pain intensity, a nerve block in the affected area should also be considered. The entire injection procedure will be performed under real-time US guidance to ensure the correct injection pathway and to reconfirm accurate needle placement (Figure 3). After the injection, patients will remain in the supine position under close observation for 15 min.

**Figure 3 fig3:**
[figure not shown]
Ultrasound-guided PRP injection. **(A)** Injection with the shoulder in the neutral position. **(B)** External rotation of the shoulder to optimize the spread of the injectate within the injured tendon.

### Study assessments

2.4

#### MRI

2.4.1

All patients will undergo 3.0 T-MRI using the Intera Achieva 3.0T MRI system (Philips), which has a reported sensitivity of 0.98 and specificity of 0.96 for the detection of tendon tears (26, 27). The scanning parameters include a field of view of 22 cm × 22 cm, a matrix size of 256 × 256, and a slice thickness of 3 mm with a 1 mm gap between valid cuts. We will collect T1-weighted and proton density-weighted fat-saturated images (axial, sagittal, and coronal) and T2-weighted and proton density-weighted fat-saturated images (axial, sagittal, and coronal). Sagittal T2-weighted images at the anterior and posterior positions will be used to measure the size of the rotator cuff tear (28). The diagnosis of RCI and the evaluation according to the Ellman classification will be independently performed by two professional radiologists based on MRI findings. Any disagreements will be resolved through consensus (29, 30).

#### US scanning

2.4.2

As a viable, convenient, and cost-effective alternative to MRI, real-time US has demonstrated high diagnostic accuracy, with reported sensitivity and specificity of 0.84 and 0.89, respectively (31, 32). All patients will undergo five musculoskeletal ultrasonography examinations with Doppler (Wisonic Clover 60) at a frequency of 5–12 MHz, performed by an experienced musculoskeletal US specialist. The diagnostic criteria for musculoskeletal US and the detection of different types of RCI will follow the methodology described by Apostolopoulos et al. (33).

The patient is positioned in a seated posture, and scanning is performed from the medial to the lateral aspect. First, the biceps brachii muscle is localized, followed by the acquisition of a cross-sectional image of the subscapularis tendon. Subsequently, the subscapularis tendon is gradually aligned with the lesser tubercle, and the patient’s shoulder is passively positioned in maximal external rotation. Next, a short-axis view of the supraspinatus tendon is acquired, during which the patient actively performs shoulder abduction and adduction to assess the tendon’s range of motion. Finally, short-axis images of the teres minor and subscapularis tendons are obtained. The supraspinatus and teres minor muscles are traced laterally to evaluate the tendon’s range of motion until the lateral border of the humeral greater tuberosity is no longer visible. Throughout the procedure, the probe orientation is continuously adjusted to optimize imaging quality, and all acquired images are systematically stored.

#### Adverse events (AEs)

2.4.3

Patients will be instructed to record any discomfort or adverse reactions occurring during the treatment and follow-up periods, regardless of their relation to the intervention. Investigators will evaluate and record each AE with respect to causality (definitely related, probably related, possibly related, possibly unrelated, or definitely unrelated), seriousness, intensity, and expectedness. AEs related to the intervention (definitely, probably, or possibly related) will be defined as treatment-related and included in the primary safety analysis. AEs will be classified by System Organ Class (SOC) according to the latest version of the Medical Dictionary for Regulatory Activities (MedDRAs) and graded from 1 to 5 based on the Common Terminology Criteria for Adverse Events (CTCAEs). All SAEs (grade 4 or 5) will be reported to the Ethics Committee of the Affiliated Hospital of Southwest Medical University and the Chinese Clinical Trial Registry within 24 h via telephone and written email. Safety results will be reported in accordance with the CONSORT Harms statement, including the incidence of total AEs, treatment-related AEs, and SAEs in each group.

The detailed AE classification and reporting framework are presented in the Supplementary file.

#### Cytokine detection

2.4.4

Peripheral blood samples (5 mL) will be collected from all participants at baseline (2 days before the PRP injection) and at 1, 3, 6, and 12 months after the first PRP injection. The blood samples will be centrifuged at 3000 rpm for 15 min to separate the serum, which will be stored at −80 °C for subsequent analysis. The concentrations of pro-inflammatory cytokines (IL-1β, IL-6, IL-8, IL-10, and TNF-*α*) in serum will be measured using enzyme-linked immunosorbent assay (ELISA) with commercially available kits (R&D Systems, USA) in strict accordance with the manufacturer’s instructions. All measurements will be performed in the central laboratory of the Affiliated Hospital of Southwest Medical University to ensure the accuracy and reproducibility of the results.

### Outcome measures

2.5

#### Primary outcome measures

2.5.1

The primary outcomes of this study are shoulder function, assessed using the Chinese version of the Constant-Murley Score (CMS), and pain intensity, assessed using the visual analog scale (VAS), both measured 12 months after the first injection. The Chinese version of the CMS has been validated in the Chinese population, demonstrating good internal consistency (Cronbach’s *α* = 0.739) and test–retest reliability (ICC = 0.827) (34). The Chinese version of the CMS consists of four domains, with a total score ranging from 0 to 100: Pain (1 item, 0–15 points), activities of daily living (ADL, 4 items, 0–20 points), mobility (4 items, 0–40 points), and strength (1 item, 0–25 points). It is a combined self-reported and examiner-based tool, with higher scores indicating better shoulder function (35). Overall shoulder pain will be assessed using the VAS, with scores ranging from 0 (no pain) to 10 (maximal pain). Follow-up time points are summarized in Table 2. Additional details of the outcomes are provided in Table 3.

**Table 2 tab2:** Schedules for follow-up assessments and data collection.

Assessments	Baseline (2 days before PRP injection)	End of injection therapy			
		1 month	3 months	6 months	12 months
Chinese version of the CMS	✓	✓	✓	✓	✓
VAS	✓	✓	✓	✓	✓
Tear size (MRI)	✓			✓	✓
US scanning	✓	✓	✓	✓	✓
Cytokine measurements	✓	✓	✓	✓	✓
SF-12	✓	✓	✓	✓	✓
AEs		✓	✓	✓	✓

**Table 3 tab3:** Summary of outcomes.

**Category**	**Outcome**	**Description**
Primary outcomes	Chinese version of the CMS	The score consists of four domains: pain (1 item, 0–15), ADL (4 items, 0–20), mobility (4 items, 0–40), and strength (1 item, 0–25), giving a total score ranging from 0 (worst) to 100 (best). Higher scores indicate better function.
	VAS	Overall shoulder pain will be assessed using the VAS, with scores ranging from 0 (no pain) to 10 (maximal pain).
Secondary outcomes	Tear size (MRI) - Ellman classification	Grade I: <3 mm, <25% tendon thickness; Grade II: 3–6 mm, 25–50% tendon thickness; Grade III: >6 mm, >50% tendon thickness.
	US scanning	Shoulder changes will be assessed by US scanning of the rotator cuff tendon integrity, acromioclavicular joints, biceps tendon, posterior labrum, and SASD bursa.
	Cytokine measurements	Changes in cytokine levels (IL-1β, IL-6, IL-8, IL-10, and TNF-α) in peripheral blood.
	SF-12	It is divided into two parts: the Mental Component Summary (MCS) and the Physical Component Summary (PCS). Each component is scored from 0 to 100, with higher scores indicating better quality of life.
	AEs	The most reported AE is post-injection pain, followed by infections. Other AEs include inflammation, allergic reactions, and nodule formation. The detailed AEs classification is displayed in Supplementary file.

#### Secondary outcome measures

2.5.2

Secondary outcomes include the following: (1) imaging changes assessed by MRI and US (36); (2) serum cytokine levels (IL-1β, IL-6, IL-8, IL-10, and TNF-α); (3) quality of life, assessed using the 12-Item Short Form (SF-12) (37); and (4) AEs (38). Follow-up time points are provided in Table 2. Additional details of the outcomes are provided in Table 3.

### Sample size

2.7

The sample size was calculated based on VAS pain scores, as this outcome exhibits the greatest variability and allows for a conservative estimate. According to a previous randomized controlled trial in patients with partial-thickness rotator cuff tears (20), the minimal clinically important difference (MCID) for the VAS is 1.4 cm, with a standard deviation (SD) of 2.41 cm. To detect this difference between the two groups at 12-month post-injection, with a two-sided significance level of *α* = 0.025 (Bonferroni-adjusted for two primary endpoints) and a power of 80% (*β* = 0.20), the required sample size per group was calculated using the formula for two independent means:

$$n=\frac{2\times {\left(Z_{\alpha /2}+Z_{\beta }\right)}^{2}\times \sigma^{2}}{\delta^{2}}$$

whereZα/2=2.24(forα/2=0.0125),Zβ=0.84(forβ=0.20),σ=2.41,andδ=1.4.This yields:

$$\begin{array}{c} n=\frac{2\times {\left(2.24+0.84\right)}^{2}\times {\left(2.41\right)}^{2}}{{\left(1.4\right)}^{2}}=\frac{2\times {\left(3.08\right)}^{2}\times 5.8081}{1.96}\\ =\frac{2\times 9.4864\times 5.8081}{1.96}\approx 56.2 \end{array}$$

Therefore, 57 participants per group are required. Assuming a 20% dropout rate over the 12-month follow-up period, the final sample size is increased to 72 participants per group, resulting in a total of 144 participants.

The study is also adequately powered for the Chinese version of the CMS, the second primary outcome. Previous studies in similar populations report an SD of approximately 15–20 points and an MCID of approximately 10 points for the CMS (35, 39). With 57 participants per group, *α* = 0.025, and 80% power, the detectable difference is calculated as follows:

$$\delta =(Z_{\alpha /2}+Z_{\beta })\times \sigma \times \sqrt{\frac{2}{n}}=(2.24+0.84)\times \sigma \times \sqrt{\frac{2}{57}}=3.08\times \sigma \times 0.187$$

With *σ* = 18, *δ* is approximately 10.4 points, and with *σ* = 15, *δ* is approximately 8.6 points. Both values are within or below the established MCID range, confirming that the sample size is sufficient to detect clinically meaningful differences in the CMS.

For secondary and exploratory outcomes (e.g., MRI findings), the study is not specifically powered. These analyses will be considered hypothesis-generating, and the results should be interpreted with caution.

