#### Primary outcome analysis

2.8.3

The primary outcomes (the Chinese version of the CMS and the VAS at 12 months) will be analyzed using analysis of covariance (ANCOVA), with treatment group as a fixed factor and baseline score, age, and time from diagnosis to injection as covariates. A Bonferroni-corrected significance level of *p* < 0.025 (two-tailed) will be applied to each primary outcome to account for multiple comparisons. The study will be considered positive if at least one primary outcome achieves statistical significance at the adjusted 
α
 level, provided that the other outcome shows consistent directional improvement.

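### The assurance that 57 per arm is enough for the second primary outcome, the CMS, does not hold across the protocol's own SD range: power for 10 points is about 91%, 77% and 67% at SD 15, 18 and 20

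*Protocol article*

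**What the plan says.** Protocol article, section 2.7 (Sample size), bases the calculation on the VAS, "as this outcome exhibits the greatest variability and allows for a conservative estimate". The inputs are an MCID "for the VAS is 1.4 cm, with a standard deviation (SD) of 2.41 cm", 80% power, and a test "with a two-sided significance level of *α* = 0.025 (Bonferroni-adjusted for two primary endpoints"). The result is 57 evaluable per arm, raised to 72 per arm (144 in total) for 20% dropout.

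The section then states that the trial has adequate power for the CMS as well. Earlier studies are said to "report an SD of approximately 15–20 points and an MCID of approximately 10 points for the CMS". Detectable differences with 57 per arm are given for SD 18 (10.4 points) and SD 15 (8.6 points), followed by: "Both values are within or below the established MCID range, confirming that the sample size is sufficient".

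Section 2.8.3 (Primary outcome analysis) uses the same error rate, 0.025 ("two-tailed) will be applied to each primary outcome to account for multiple comparisons"), and plans ANCOVA with baseline score, age and time from diagnosis to injection as covariates. The trial counts as positive if at least one primary outcome is significant and the other points the same way.

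**The concern.** The concluding sentence disagrees with the figures just before it in three ways.

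- It appeals to an MCID range, but the section gives a single value of about 10.
- One of the two detectable differences, 10.4, is above that value.
- The cited SD range runs to 20, but the calculation stops at 18, so the least favourable case is not shown.

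The reason for sizing on the VAS is also doubtful. Required sample size depends on the ratio of SD to target difference, not on variability alone, and over part of the cited range that ratio is larger for the CMS.

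The CMS is one of two primary outcomes. If its SD turns out near 20, the chance of missing a true 10-point difference is about one in three, not the one in five implied. A non-significant CMS result would then be read against a published assurance that the sample was large enough.

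**Working it through.** **Inputs, all from section 2.7.** VAS: δ = 1.4, σ = 2.41. CMS: MCID about 10, σ about 15 to 20. Two-sided α = 0.025 (z = 2.24; 2.2414 unrounded). Power 80% (z = 0.84; 0.8416 unrounded). n = 57 evaluable per arm.

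**1. The protocol's own figures reproduce.**

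- VAS: n = 2 × 3.08² × 2.41² / 1.4² = 56.2, so 57. Then 57 / 0.8 = 71.25, so 72 per arm and 144 in total.
- CMS: δ = 3.08 × σ × √(2/57), with √(2/57) = 0.1873. At σ = 18, δ = 10.38. At σ = 15, δ = 8.65 (8.64 with the protocol's rounded 0.187, hence its 8.6).

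**2. The same formula at the omitted SD.** At σ = 20, δ = 3.08 × 20 × 0.1873 = 11.54 points.

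**3. Power for 10 points with 57 per arm.** Power = Φ(10 / (σ√(2/57)) − 2.2414). Sample size for 80% power: n = 2 × (2.2414 + 0.8416)² × σ² / 10².

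| CMS SD | Detectable difference at 80% | 10 / (σ√(2/57)) | Power, normal | Power, noncentral t | n per arm for 80% |
|---|---|---|---|---|---|
| 15 | 8.7 | 3.559 | 90.6% | 89.9% | 43 |
| 18 | 10.4 | 2.966 | 76.6% | 75.5% | 62 |
| 20 | 11.5 | 2.669 | 66.6% | 65.5% | 77 |

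(At SD 20 the unrounded n is 76.04, so 77; the rounded 3.08 gives 75.9, so 76.)

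**4. Which outcome is more demanding.** SD/MCID is 2.41 / 1.4 = 1.72 for the VAS. For the CMS it is 1.50, 1.80 and 2.00 at SD 15, 18 and 20. The two are equal at a CMS SD of 10 × 1.72 = 17.2. Below that the VAS needs more patients; above it the CMS does.

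**5. What ANCOVA could recover.** With a baseline to 12-month correlation ρ, the residual SD is about σ√(1 − ρ²). Under the normal approximation, 80% power for 10 points needs a residual SD of at most 10 / (3.083 × 0.1873) = 17.3.

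- SD 18: ρ = √(1 − (17.3/18)²), about 0.27 (0.31 on the t distribution).
- SD 20: ρ = √(1 − (17.3/20)²), about 0.50 (0.52 on the t distribution).

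The protocol gives no value for ρ. If it were 0.3 to 0.5, power would be about 81% to 88% at SD 18 and 71% to 80% at SD 20.

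**6. If nobody drops out.** With all 72 per arm evaluable, power is about 86% at SD 18 and 78% at SD 20.

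**The case against.** **The gap is rounding.** Both the MCID and the SD are described as approximate, and 10.4 against about 10 is 0.4 points on a 100-point scale. This stands for SD 18, where the loss is about 3 points of power. At the midpoint of the range, SD 17.5, power is 79%. It does not stand for SD 20, where the detectable difference is 11.5 and power is 67%.

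**The planned analysis is ANCOVA, so unadjusted power is pessimistic.** It probably is. But section 2.7 uses the unadjusted formula and assumes no correlation, so its sentence cannot rest on that gain. At SD 20 the correlation would have to be about 0.5.

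**One significant primary outcome is enough.** This limits the consequence. If the true differences are 1.4 on the VAS and 10 on the CMS, and the two test statistics correlate at 0.3 to 0.7 (an assumption), at least one is significant with probability about 88% to 93% at SD 18 and 85% to 90% at SD 20, before the directional condition. It does not make the statement about the CMS correct. Nor does the protocol plan to conclude equivalence from a null CMS result, so over-reading such a result is a risk of interpretation, not a planned step.

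**Stronger readings that the documents do not support.**

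- A reader might infer that the VAS is simply the wrong outcome to size on. It is the more demanding one for any CMS SD from 15 to about 17.2.
- A reader might infer that 144 patients is a miscalculation. The VAS calculation reproduces.
- A reader might infer a fault in the multiplicity rule. Bonferroni at 0.025 is valid, and sections 2.7 and 2.8.3 agree on it.

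**Conclusion.** The claim of adequate power for the CMS is wrong as written. It holds in the lower part of the cited SD range (91% at SD 15), falls slightly short at the protocol's own SD of 18 (77%), and falls well short at the upper bound that the protocol cites but does not evaluate (67%). The description of the VAS as the conservative basis is true only for a CMS SD below about 17.2.

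These figures assume 57 evaluable patients per arm, a true difference of exactly 10 points, a two-sided 0.025 test and no covariate adjustment, as in section 2.7. The point concerns one incorrect statement about one primary outcome. It does not show that the trial as a whole is underpowered under its at-least-one success rule, or that the enrolment target must change.

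**What to change.** In section 2.7:

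1. Report the CMS at SD 15, 18 and 20: detectable differences of about 8.7, 10.4 and 11.5 points at 80% power, and unadjusted power for 10 points of about 91%, 77% and 67%.
2. Delete the sentence containing "Both values are within or below the established MCID range, confirming that the sample size is sufficient", and limit the preceding adequacy claim to the SDs for which it holds.
3. Delete the rationale "as this outcome exhibits the greatest variability and allows for a conservative estimate", or qualify it by saying that the VAS is the more demanding outcome only for a CMS SD below about 17.2.
4. If ANCOVA is relied on to reach 80%, state the assumed baseline correlation: about 0.3 at SD 18 and about 0.5 at SD 20.

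The cost is a few sentences and a less favourable stated power for the CMS. No extra patients are needed.

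Holm in place of Bonferroni is optional and not part of this correction. It would keep the 5% familywise error rate, but it changes the testing procedure, its gain depends on a real VAS effect, and even with a VAS effect of 1.4 it leaves CMS power near 74% at SD 20.

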### Statistical analysis

2.8

Statistical analyses will be performed using SPSS 25.0 (IBM Corporation, Armonk, NY, USA) and R 4.0 (R Foundation for Statistical Computing, Vienna, Austria) by an independent statistician ([name]) who will remain blinded to treatment allocation until all primary analyses are completed. The intention-to-treat (ITT) principle will be applied to all primary analyses, including all randomized participants who will receive at least one PRP injection. A per-protocol (PP) analysis will be conducted as a sensitivity analysis, excluding participants with major protocol violations.

#### Descriptive statistics

2.8.1

Continuous variables will be summarized as mean 
±
SD or median with interquartile range (IQR). Categorical variables will be presented as frequencies and percentages (*n* %). Normality will be assessed using the Shapiro–Wilk test, and homogeneity of variance will be examined with Levene’s test.

#### Baseline comparability

2.8.2

Baseline characteristics will be compared between the groups using independent-samples *t*-tests or the Mann–Whitney *U*-test for continuous variables and chi-squared tests or Fisher’s exact test for categorical variables. Variables showing between-group differences at a *p*-value of <0.10 will be included as covariates in adjusted analyses.

#### Primary outcome analysis

2.8.3

The primary outcomes (the Chinese version of the CMS and the VAS at 12 months) will be analyzed using analysis of covariance (ANCOVA), with treatment group as a fixed factor and baseline score, age, and time from diagnosis to injection as covariates. A Bonferroni-corrected significance level of *p* < 0.025 (two-tailed) will be applied to each primary outcome to account for multiple comparisons. The study will be considered positive if at least one primary outcome achieves statistical significance at the adjusted 
α
 level, provided that the other outcome shows consistent directional improvement.

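### Testing both primary outcomes at a flat Bonferroni 0.025 is valid, but the Holm procedure would give more power to confirm both at the same 5% familywise error and with no added patients

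*Protocol article*

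**What the plan says.** Section 2.8.3 (Primary outcome analysis) analyses CMS and VAS at 12 months by ANCOVA and holds each to 0.025: "two-tailed) will be applied to each primary outcome to account for multiple comparisons". The level for one outcome does not depend on the result for the other.

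The success rule follows: "The study will be considered positive if at least one primary outcome achieves statistical significance at the adjusted" level, "provided that the other outcome shows consistent directional improvement".

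Section 2.7 (Sample size) uses the same level, "0.025 (Bonferroni-adjusted for two primary endpoints"), with 80% power. For VAS it takes as given that "the minimal clinically important difference (MCID) for the VAS is 1.4 cm, with a standard deviation (SD) of 2.41 cm", and concludes that "57 participants per group are required", or 72 after 20% dropout. For CMS it says that earlier studies "report an SD of approximately 15–20 points and an MCID of approximately 10 points for the CMS", and works through SDs of 18 and 15. No step-down or other sequential procedure appears in the article.

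**The concern.** A flat split uses half of the 5% error on each outcome even after one null hypothesis has been rejected. At that point at most one true null can remain, so the other outcome could be tested at the full 0.05 without exceeding 5% overall. Suppose VAS gives p = 0.01 and CMS gives p = 0.04. Under section 2.8.3 the trial may not claim an effect on function, although that claim would be valid at 5% familywise error. At stake is the power to make a formal claim on the second of two named primary outcomes.

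**Working it through.** **1. The plan's own figures.** VAS: n = 2 × (2.24 + 0.84)² × 2.41² / 1.4² = 56.2, so 57 per arm; 57 / 0.80 = 71.25, so 72. CMS detectable difference: 3.08 × SD × √(2/57) = 10.4 at SD 18 and 8.65 at SD 15. These agree with section 2.7.

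**2. Why Holm is valid.** If both nulls are true, an error needs the smaller p below 0.025, which has probability at most 2 × 0.025 = 0.05. If one null is true, rejecting it needs its own p below 0.05 at the least. This holds under any dependence. In simulation with VAS real and CMS null, CMS was falsely rejected in 3.9–4.5% of trials under Holm and 2.5% under Bonferroni. With both null, the chance of any false rejection is the same for both rules and at most 5%.

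**3. Inputs for power.** From section 2.7: 57 per arm, VAS 1.4 with SD 2.41, CMS 10 with SD 15, 18 or 20. Assumed: true effects equal the MCIDs, and a correlation ρ of 0.3–0.7 between the two test statistics (each signed so that benefit is positive). The article gives no correlation.

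The mean of each statistic is m = δ / (SD × √(2/n)), with √(2/57) = 0.1873:
- VAS: 1.4 / (2.41 × 0.1873) = 3.10
- CMS: 3.56 (SD 15), 2.97 (SD 18), 2.67 (SD 20)

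Critical values are 2.241 (0.025) and 1.960 (0.05).
- Bonferroni, both: P(Z₁ > 2.241, Z₂ > 2.241)
- Holm, both: P(Z₁ > 2.241, Z₂ > 1.960) + P(Z₁ > 1.960, Z₂ > 2.241) − P(Z₁ > 2.241, Z₂ > 2.241)

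Hand check at ρ = 0, SD 18. Single-outcome powers are 0.805 (VAS) and 0.766 (CMS) at 0.025, and 0.873 and 0.843 at 0.05. Bonferroni: 0.805 × 0.766 = 0.616. Holm: 0.805 × 0.843 + 0.873 × 0.766 − 0.616 = 0.731.

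**4. Power to confirm both, 57 per arm (Bonferroni → Holm, %).**

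| CMS SD | ρ 0.3 | ρ 0.5 | ρ 0.7 |
|---|---|---|---|
| 15 | 74.6 → 83.0 | 75.9 → 83.8 | 77.6 → 84.7 |
| 18 | 64.4 → 74.7 | 66.6 → 76.1 | 69.3 → 77.8 |
| 20 | 56.8 → 67.8 | 59.2 → 69.5 | 61.9 → 71.4 |

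The gain runs from 7.1 to 11.1 points.

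**5. Each outcome alone (SD 18, ρ 0.5).** CMS rises from 76.6% to 81.9%, and VAS from 80.5% to about 85%. That is about 5 points each.

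**6. At least one outcome.** The first Holm step is the Bonferroni test, so this power is identical under both rules: 90.4% at SD 18, ρ 0.5.

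**7. Sensitivity (ρ 0.3–0.7).**
- ANCOVA with an assumed correlation of 0.5 between baseline and 12 months multiplies each SD by √(1 − 0.25) = 0.866. The gain is then 4.7–4.0 points (SD 15), 6.9–5.6 (SD 18) and 8.5–7.2 (SD 20).
- All 72 per arm evaluable, SDs unadjusted: 5.4–4.6, 7.6–6.2 and 9.1–7.7 points.

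**The case against.** The strongest reply is that nothing here is wrong. Flat Bonferroni controls the familywise error, was fixed in advance, and agrees with the sample size. The success rule asks for one significant outcome and only a consistent direction on the other, so the trial never sets itself the goal of confirming both. The example with p = 0.01 and p = 0.04 would already be a positive trial if both effects point the same way. Bonferroni also keeps each 97.5% interval in step with its test, which Holm with simple intervals does not. All of this stands. It limits the point to lost efficiency on a second claim, but gives no gain in error control for keeping the flat rule.

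A reader might infer more, and the documents do not support it:
- **That the error rate is mishandled or the sample size is wrong.** Neither follows. The first Holm step is still 0.025, so section 2.7 is untouched.
- **That the loss is worse because CMS contains a pain domain and so moves with VAS.** The reverse is true. Holm's advantage does not need any link, and correlation shrinks it: at SD 18 the gain falls from 11.4 points at ρ = 0 to 7.8 at ρ = 0.8.
- **That Holm secures 80% power for CMS throughout the stated SD range.** At SD 20 and ρ 0.5 CMS power rises only from 66.6% to 73.7%.

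**Conclusion.** The point holds as a cheap gain in efficiency, not as an error in the plan. On the protocol's own effects and SDs, flat Bonferroni gives up about 7–11 points of power to confirm both outcomes, and about 5 points for each outcome alone at SD 18. The size depends on true effects equal to the MCIDs, 57 evaluable per arm, and a correlation the article does not give. Baseline adjustment or lower dropout would reduce it to the ranges in the sensitivity check. The chance of declaring the trial positive is unaffected.

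**What to change.** In section 2.8.3, replace the Bonferroni sentence with: *The two primary outcomes are tested by the Holm procedure at a two-sided familywise alpha of 0.05: the smaller p-value at 0.025 and, if significant, the other at 0.05.*

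The success rule must change with it, because its reference to an adjusted level could then mean 0.025 or 0.05: *at least one primary outcome significant under the Holm procedure (smaller p < 0.025)*, with the directional proviso kept. Section 2.7 needs no change.

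The cost is two sentences, written before any outcome data are seen, and no patients. The downside is in reporting: a simple 97.5% interval may include zero for an outcome claimed at the second step (CMS at p = 0.04, for instance). The report should therefore say that the claims rest on the Holm test.
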